### Evaluation of adherence

Adherence to the interventions (shoe inserts and rehabilitation therapy) in both groups will be assessed at monthly intervals up to 52 weeks via postal survey. For the shoe insert interventions, participants will provide information regarding the number of hours per day and number of days that they have worn their inserts during the previous 4 weeks. For the rehabilitation therapy intervention, participants will provide information regarding the average number of days per week that they have performed their exercises during the previous 4 weeks. To minimise participant burden, adherence will be documented on the day with recall over the previous 4 weeks, rather than by daily diary entries [14, 46, 47].

A summary of the data collection time points for each of the outcome measures is shown in Fig. 4.

**Fig. 4 Fig4:**
[figure not shown]
SPIRIT (Standard Protocol Items: Recommendations for Interventional Trials) diagram of enrolment, interventions and assessments for the SIMPLE trial

### Adverse events

Adverse events from the shoe insert(s) and rehabilitation therapy (such as skin blistering or the occurrence of new pain or injuries in other areas of the foot and body) will be assessed at monthly intervals up to 52 weeks via postal survey. Participants will be asked to document the type of adverse event, the body location, the frequency and/or severity of the event [14, 46, 47]. If participants experience more significant adverse events (e.g. severe pain), they will be advised to contact one investigator who is not involved in recruitment, allocation or data collection ([name], [name], [name]). All adverse events will be reported in the final manuscript.

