**Methods:**

Ninety participants with first MTPJ OA will be randomised to receive full-length shoe-stiffening insert(s) (Carbon Fibre Spring Plate, Paris Orthotics, Vancouver, BC, Canada) plus rehabilitation therapy or sham shoe insert(s) plus rehabilitation therapy. Outcome measures will be obtained at baseline, 4, 12, 24 and 52 weeks; the primary endpoint for assessing effectiveness being 12 weeks. The primary outcome measure will be the foot pain domain of the Foot Health Status Questionnaire (FHSQ). Secondary outcome measures will include the function domain of the FHSQ, severity of first MTPJ pain (using a 100-mm Visual Analogue Scale), global change in symptoms (using a 15-point Likert scale), health status (using the Short-Form-12® Version 2.0 and EuroQol (EQ-5D-5L™) questionnaires), use of rescue medication and co-interventions, self-reported adverse events and physical activity levels (using the Incidental and Planned Activity Questionnaire). Data will be analysed using the intention-to-treat principle. Economic analysis (cost-effectiveness and cost-utility) will also be performed. In addition, the kinematic effects of the interventions will be examined at 1 week using a three-dimensional motion analysis system and multisegment foot model.

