### Design

This study is a parallel-group, participant- and assessor- blinded, randomised controlled trial with a 52-week follow-up (Fig. 1). Participants will be randomised to an experimental group (shoe-stiffening insert(s) (Carbon Fibre Spring Plate, Paris Orthotics, Vancouver, BC, Canada) or a control group (sham shoe insert(s)). To ensure that all participants, who will have some level of pain and disability, receive some form of intervention, both groups will also be prescribed the same rehabilitation therapy programme. This design covers any ethical concerns of not treating participants in pain, but will allow the effectiveness of the shoe-stiffening inserts to be evaluated.

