#### Inclusion criteria

To be included in this study, participants must: (1) be aged at least 18 years, (2) report having pain in the first MTPJ on most days for at least 12 weeks, (3) report having pain rated at least 30 mm on a 100-mm Visual Analogue Scale (VAS), (4) have pain upon palpation of the dorsal aspect of the first MTPJ and restricted first MTPJ dorsiflexion (less than 64° of dorsiflexion range of motion) [26], (5) be able to walk household distances (more than 50 m) without the aid of a walker, crutches or cane, (6) be willing to have their foot X-rayed, (7) agree to attempt to not receive additional interventions (such as shoe modifications, physiotherapy, foot orthoses, intra-articular injections, or surgery) for the first MTPJ pain during the course of the study, (8) be able to reach their feet to perform ‘rehabilitation therapy’ of the first MTPJ and (9) be willing to attempt to discontinue consuming any pain relieving medications for first MTPJ OA (except paracetamol (up to 4 g per day) which will be rescue medication) for at least 14 days prior to the baseline assessment and during the study period. Participants who consume paracetamol for first MTPJ pain prior to recruitment will be advised to discontinue its use at least 24 h prior to the baseline assessment and follow-up assessments at 4, 12, 24 and 52 weeks.

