### Statistical analysis

Statistical analysis will be performed using the most recent version of SPSS (IBM Corp., Armonk, NY, USA) available at the time of analysis. Analysis will adhere to the intention-to-treat principle for all randomised participants. In participants with bilateral symptoms, the more painful foot will be analysed (or the right foot if they cannot define the more painful foot) to maintain independence of data. Multiple imputation will be used to replace any missing data using five iterations, with sex, age, baseline scores and group allocation as predictors. The exception will be for the following variables where no data substitution will be applied: self-reported magnitude of symptom change, use of co-interventions, and adverse events. Standard tests to assess continuous data for normal distribution will be used and transformation carried out if required. The primary outcome measure will be the foot pain domain of the FHSQ measured at 12 weeks. To avoid over-testing and to minimise the risk of type I error associated with serial measurements, statistical analysis of the effectiveness of the interventions will specifically focus on the change in primary outcome measures between baseline and 12 weeks [55, 56], and differences in the primary and secondary outcome measures between the two groups will be compared at 12 weeks. Continuously scored outcome measures (FHSQ foot pain domain, FHSQ foot function domain, severity of pain at the first MTPJ whilst walking over a flat surface and during rest in the previous week, level of physical activity using the IPAQ, and health status using the SF-12® and EQ-5D-5L™) will be analysed using analysis of covariance with the intervention group and baseline scores entered as independent variables. Self-reported magnitude of symptom change will be compared using relative risk, risk difference and number needed to treat (NNT). Use of paracetamol rescue medication and intervention adherence will be compared using independent groups *t* tests. Use of co-interventions and frequency of adverse events will be compared using relative risk and risk difference statistics. For the biomechanical evaluation, first MTPJ range of motion and maximum first MTPJ dorsiflexion will be compared between groups using analysis of covariance with the intervention group and shoe-only condition scores entered as independent variables.

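### The monthly survey asks for adverse events arising from the study treatments but all events are promised in the report; collect events whatever their cause and record the suspected source

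*Protocol article*

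**What the plan says.** All references are to the protocol article.

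- **Adverse events, scope.** The monthly postal survey, running to 52 weeks, covers "Adverse events from the shoe insert(s) and rehabilitation therapy (such as skin blistering or the occurrence of new pain or injuries in other areas". The sentence goes on to include the rest of the foot and the body.
- **Adverse events, items recorded.** "Participants will be asked to document the type of adverse event, the body location, the frequency and/or severity of the event". Suspected source is not listed.
- **Adverse events, reporting.** "All adverse events will be reported in the final manuscript". Participants with more significant events are also advised to contact an investigator.
- **Abstract, Methods.** The outcome is given without any causal limit: "self-reported adverse events and physical activity levels".
- **Statistical analysis.** "Use of co-interventions and frequency of adverse events will be compared using relative risk and risk difference statistics". No breakdown by source is mentioned.
- **Design.** "both groups will also be prescribed the same rehabilitation therapy programme".
- **Inclusion criteria.** Participants agree to try to stop other pain-relieving medication, "except paracetamol (up to 4 g per day) which will be rescue medication". Under Secondary outcome measures its use is recorded by monthly diary; harms from it are not mentioned.

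**The concern.** The scope sentence names two causes. If the survey form follows it, an event is reported only when someone has already linked it to the insert or the exercises, and the person completing a postal form is the participant. The insert changes shoe stiffness considerably: Sham inserts (control group) gives 0.208 Nm/deg against 0.027 for the shoe alone. Biomechanical evaluation measures the hip, knee and ankle as well as the toe joint. Pain at a distant joint is therefore a plausible harm, and one that a participant may not connect with an insert. An event from the rescue drug lies outside both named causes.

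The listed items also give no reliable way to separate insert events from exercise events afterwards. The exercise programme applies heat, cold and self-mobilisation to the same foot that wears the insert, so type and location will often leave the source open. Source information not collected at the time is hard to recover later.

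At stake is the between-arm comparison of harms, the main safety evidence the trial will give on the device.

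**Working it through.** **No planned figure to reproduce.** The article gives no adverse event rate and no power statement for harms. The only figure used from it is the total of 90 participants (Sample size), taken as 45 per arm before dropout.

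**Step 1: the wordings side by side.** The scope sentence limits events to those from two treatments. The closing sentence and the abstract set no such limit. The examples in the scope sentence cover the whole body, so location is not restricted; what is restricted is cause. A promise to report all events can cover only events that were collected. The sentences therefore agree only if the form asks for events of any cause, which the scope sentence does not say.

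**Step 2: effect of attribution on the comparison.** Let *p1* and *p0* be the true risks of an event in the insert and sham arms, and *s1* and *s0* the shares of affected participants who link their event to a treatment and so report it.

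- Reported relative risk = (*s1* × *p1*) / (*s0* × *p0*) = true relative risk × (*s1* / *s0*).
- If *s1* = *s0* = *s*, the relative risk is unchanged and the risk difference becomes *s* × (*p1* − *p0*), smaller than the truth.
- If *s1* and *s0* differ, both measures shift.

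The article gives nothing from which to estimate *s*, so the size of this effect is unknown. Asking for events of any cause takes *s* out of the comparison.

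**Step 3: effect of events from the shared exercises.** Let *a1* and *a0* be the risks of an insert-related event and *q* the risk of an exercise-related event, assumed equal in both arms and independent of the first.

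- Risk of any event = 1 − (1 − *a*)(1 − *q*).
- Risk difference = (1 − *q*)(*a1* − *a0*).

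All rates below are assumptions.

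*First illustration: a1 = 20%, a0 = 5%, q = 30%.*

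- Insert events alone: 0.20 / 0.05 gives relative risk 4.0; the risk difference is 15 points.
- Any event: 1 − 0.80 × 0.70 = 0.440 against 1 − 0.95 × 0.70 = 0.335. Relative risk 0.440 / 0.335 = 1.31; risk difference 10.5 points (0.70 × 15).

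*Second illustration: a1 = 30%, a0 = 10%, over a range of q. Power is for a two-sided 5% comparison of two proportions with 45 per arm (normal approximation).*

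| q | Any event, insert v sham | Relative risk | Risk difference (points) | Power |
|---|---|---|---|---|
| 0% | 30% v 10% | 3.00 | 20 | 0.67 |
| 10% | 37% v 19% | 1.95 | 18 | 0.48 |
| 20% | 44% v 28% | 1.57 | 16 | 0.35 |
| 30% | 51% v 37% | 1.38 | 14 | 0.27 |
| 50% | 65% v 55% | 1.18 | 10 | 0.16 |

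The relative risk moves quickly towards 1. The risk difference shrinks only by the factor (1 − *q*).

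**Step 4: what all-cause collection adds.** Take the first illustration and add unrelated events in an assumed 20% of each arm. Any event is 1 − 0.560 × 0.80 = 0.552 against 1 − 0.665 × 0.80 = 0.468: relative risk 1.18, risk difference 8.4 points. Collecting more events therefore dilutes the relative risk further. This is why the risk difference needs to be shown beside it.

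**The case against.** The strongest reply is that the text is less restrictive than its opening words suggest. The examples reach the whole body, so knee, hip or back pain fits them. The section closes by promising all events, and the abstract sets no causal limit. The survey form is not shown, and no causality question is described. This stands, and it rules out saying that events count only if attributed, or that unattributed harms are lost. What remains is that the statements disagree, so events may be missed.

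On the rescue drug, paracetamol is permitted as an exception to stopping other pain relief. Nothing directs participants to take it through the trial. That also stands; the point is only that its harms lie outside the stated survey scope.

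On pooling, a reader might infer that insert and exercise events are planned as one composite. The article says only that "frequency of adverse events will be compared using relative risk and risk difference statistics"; it neither specifies a composite nor excludes a breakdown. Type and body location are recorded, so some tabulation would be possible, and the analysis plan may provide it. Pooling is an inference from the lack of a stated split.

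On dilution, exercise events occur in both randomised arms. They add noise to the contrast without confounding it, and the planned risk difference falls much less than the relative risk.

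Finally, all-cause counting increases dilution (Step 4), and a comparison restricted by suspected source brings back the lay attribution that caused the difficulty. Both are correct. They are the reason for keeping the all-cause comparison as the main one and the source breakdown descriptive.

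**Conclusion.** The point holds in a limited form. The scope sentence and the closing promise in Adverse events disagree and must be reconciled. Under the scope sentence as written, events that a participant does not link to a study treatment, and events from rescue paracetamol, may go unrecorded; suspected source is not among the items listed.

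The size of any under-recording is unknown, because the article gives no event rates and the form is not shown. The dilution figures (relative risk 4.0 to 1.31, risk difference 15 to 10.5 points) rest on assumed rates, independence of the two kinds of event and equal exercise risk in both arms. They show that the relative risk alone would be a poor summary.

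A reader might go further and conclude that the planned comparison is biased towards finding no difference. The documents do not support that: shared events do not bias a randomised contrast, and nothing in them shows that attribution differs between arms.

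**What to change.** 1. Reword Adverse events so that the survey scope matches the closing promise.
2. Have the monthly form ask for every new pain, skin problem, injury or illness since the last form, whatever its cause.
3. For each event add one tick-box for suspected source: insert, rehabilitation therapy, pain medicine, other or unsure. The same monthly postal approach already asks about inserts and exercises separately under Evaluation of adherence, so the distinction is workable.
4. Make the main harm analysis the all-cause comparison of participants with at least one event, by randomised arm, with the risk difference beside the relative risk.
5. Report events by suspected source, type and body location in a secondary descriptive table.
6. Trial status gives the first enrolment as 16 June 2016. If forms have already been returned, state in the report what question was asked, and do not reconstruct source afterwards.

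The cost is one reworded question, one tick-box and one table. The downside is more unrelated minor events. Randomisation and participant blinding should spread these evenly between arms, but they add noise and pull the relative risk towards 1.

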### Biomechanical evaluation

Biomechanical evaluation will be performed to evaluate change in biomechanical function of the first MTPJ using the shoe-stiffening inserts as this is the proposed mechanism of action of the shoe-stiffening inserts. Measurement of first MTPJ kinematic variables (range of motion of first MTPJ and maximum first MTPJ dorsiflexion) will be performed during level walking, in addition to kinematic and kinetic analysis of the hip, knee and ankle. These assessments will be performed at 1 week, rather than baseline, to minimise participant burden and allow for some level of habituation [36]. Three-dimensional kinematics will be measured using a 10-camera infrared motion analysis system (Vicon Motion Systems Ltd., Oxford, UK). Two force plates (Kistler, 9865B, Winterthur, Switzerland and AMTI OR6, Watertown, MA, USA) will be used to identify gait cycle events and record kinetic data. Six passive retro-reflective markers will be attached to the medial forefoot (three markers) and proximal phalanx of the hallux (three markers) as required for calculation of first MTPJ kinematics using the Salford Foot Model [48]. The Salford Foot Model is a validated five-segment model that allows calculation of the kinematics of the calcaneus relative to the tibia, the midfoot relative to the calcaneus, the lateral forefoot and medial forefoot segments relative to the midfoot, and the hallux relative to the medial forefoot. In this study, the kinematics of the hallux relative to the medial forefoot will be focussed on in the analysis. This model has been used to assess first MTPJ kinematics with acceptable reliability [49]. Marker trajectories (100 Hz) and force plate (4000 Hz) data will be collected synchronously using Vicon Nexus software (Vicon Motion Systems Ltd., Oxford, UK). In addition, 32 markers will be fixed to anatomical landmarks of the trunk, pelvis and lower limb based on the modified Helen Hayes marker set [50, 51], as well as a customised model to allow for segmental definition and functional joint calibration. All lower-limb joint kinematics will be calculated based on Euler angles and described in terms of movement of the distal segment relative to the proximal segment. Data will be collected and averaged from the middle stride of six 10-m walking trials for each condition. Comparisons between intervention groups will be made for differences with and without the intervention (shoe-stiffening insert or sham insert) with participants wearing ‘gait shoes’ (canvas ‘Now’ and ‘IND99’ shoes, Kmart Australia – shoes are the same but have different branding), which comprise a laced fastening and canvas upper, and are customised with cut-outs of the upper in order to allow clear visualisation of the foot markers (Fig. 5). It is not possible to perform kinematic analysis of foot function using participants’ own closed-in shoes due to the need to attach retro-reflective markers to the foot landmarks. These analyses will be adequately powered (power >0.8 assuming *n* ≥30 and standard deviation (SD) = 7.5 [8]) to detect a difference of 5.5° in first MTPJ dorsiflexion range of motion between the interventions.

**Fig. 5 Fig5:**
[figure not shown]
Marker placement for measurement of first metatarsophalangeal joint (MTPJ) kinematics. The effect of the inserts on first MTPJ kinematics will be performed using the Salford Foot Model with participants wearing ‘gait shoes’ that have been customised with cut-outs of the upper in order to allow clear visualisation of the foot markers. *Upper panel*: medial view; *Lower panel*: lateral view

### Economic evaluation

The economic analysis will take a health service perspective, assessing the difference in health sector costs and comparing this with the difference in health outcomes between treatment and comparison groups. Participants’ time costs will be similar between both groups and do not affect the comparison. Collection of health service resource use will be informed by the Australian Guidelines for Preparing Submissions to the Pharmaceutical Benefits Scheme [52]. Participants will be asked to document their health service use, use of co-interventions, days unable to work and impairments in physical activity due to first MTPJ OA in the 4 weeks prior to each survey round (monthly intervals up to 12 months). Service encounters (e.g. GP consultations) will be converted to costs using the Pharmaceutical Benefits Advisory Committee (PBAC) Manual of Resource Items [53]. Both the cost-effectiveness and the cost-utility of the intervention will be determined: the latter as it allows comparisons of economic value with a broader range of health service interventions. The cost-effectiveness analysis will estimate the additional (or incremental) cost per person achieving a meaningful improvement in the FHSQ pain score (i.e. larger than the minimal important difference). The cost-utility analysis will use the results from the EQ-5D-5L™ to generate a health-related quality of life utility score at baseline and trial follow-up, which will be used to estimate change across the two groups. From this, an incremental cost per quality-adjusted life year will be derived. Probabilistic sensitivity analyses will be conducted, incorporating confidence limits on the plausible range of costs and effects used in the analysis.

### Sample size

The sample size has been determined a priori using SPSS Sample Power 3.0 (IBM Corp., Armonk, NY, USA) based on the FHSQ pain domain as the primary outcome measure. Using a power of 90%, minimal important difference of 12.5 points in the foot pain domain of the FHSQ [37, 54], SD of 16.8 (based on the 12-week time point in our recent trial [14]), assuming a 10% dropout rate, and a significance level set at *α* < 0.05, we estimated that a total of 90 participants will be required.

### Statistical analysis

Statistical analysis will be performed using the most recent version of SPSS (IBM Corp., Armonk, NY, USA) available at the time of analysis. Analysis will adhere to the intention-to-treat principle for all randomised participants. In participants with bilateral symptoms, the more painful foot will be analysed (or the right foot if they cannot define the more painful foot) to maintain independence of data. Multiple imputation will be used to replace any missing data using five iterations, with sex, age, baseline scores and group allocation as predictors. The exception will be for the following variables where no data substitution will be applied: self-reported magnitude of symptom change, use of co-interventions, and adverse events. Standard tests to assess continuous data for normal distribution will be used and transformation carried out if required. The primary outcome measure will be the foot pain domain of the FHSQ measured at 12 weeks. To avoid over-testing and to minimise the risk of type I error associated with serial measurements, statistical analysis of the effectiveness of the interventions will specifically focus on the change in primary outcome measures between baseline and 12 weeks [55, 56], and differences in the primary and secondary outcome measures between the two groups will be compared at 12 weeks. Continuously scored outcome measures (FHSQ foot pain domain, FHSQ foot function domain, severity of pain at the first MTPJ whilst walking over a flat surface and during rest in the previous week, level of physical activity using the IPAQ, and health status using the SF-12® and EQ-5D-5L™) will be analysed using analysis of covariance with the intervention group and baseline scores entered as independent variables. Self-reported magnitude of symptom change will be compared using relative risk, risk difference and number needed to treat (NNT). Use of paracetamol rescue medication and intervention adherence will be compared using independent groups *t* tests. Use of co-interventions and frequency of adverse events will be compared using relative risk and risk difference statistics. For the biomechanical evaluation, first MTPJ range of motion and maximum first MTPJ dorsiflexion will be compared between groups using analysis of covariance with the intervention group and shoe-only condition scores entered as independent variables.

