Poor adherence by participants to their shoe insert intervention and/or rehabilitation therapy programme has the potential to confound the study results. In our previous case series study, adherence to the shoe-stiffening inserts was excellent, with the shoe-stiffening inserts being reported to be worn for a mean of 42 h per week at 3 months [18]. Furthermore, in a previous trial investigating the effectiveness of a 4-week clinician-administered rehabilitation therapy programme for first MTPJ OA by Shamus et al. [13], adherence was reported to be 100%. Therefore, we anticipate that adherence to our interventions will be satisfactory in the short to intermediate term in our trial (12 weeks). Participant adherence may reduce over the course of this trial given its extended duration (52 weeks). However, to maximise adherence, participants will be (1) telephoned at monthly intervals to remind them to perform the rehabilitation programme and (2) asked to complete diary entries regarding the use of their shoe inserts and completion of the rehabilitation programme that will be returned at monthly intervals.

This trial will incorporate five repeated measurements for the primary outcome measure (baseline, 4, 12, 24 and 52 weeks) to provide insights into the trajectory of any improvements in symptoms. The three previous clinical trials investigating nonsurgical interventions for first MTPJ OA have used study durations of 4 [13], 12 [14] and 24 [37] weeks. Incorporating a 52-week follow-up period is a major strength of our study as it will enable us to determine the short- (4 weeks), intermediate- (12 weeks) and longer-term (24 and 52 weeks) effects of the shoe-stiffening inserts, if any. A 52-week follow-up is also important to allow the capture of important costs and effects for the planned economic analysis [57].

This will be the first trial to perform an economic analysis of any nonsurgical intervention for first MTPJ OA. Inclusion of such an analysis is important because the acceptance and use of novel interventions is determined by their cost as well as by their clinical effectiveness [58]. Results from this study will, therefore, be of value to both clinicians and health care policy-makers. Recruitment of participants will commence in April 2016 and final results are expected to be available in December 2018.

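### Missing insert-wear and exercise adherence is imputed without any information on stopping, so reported adherence can be too high; count zero from a known stop and add a zero bound

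*Protocol article*

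**What the plan says.** The Statistical analysis section gives one general rule for missing values: "Multiple imputation will be used to replace any missing data using five iterations, with sex, age, baseline scores and group allocation as predictors". It then lists the variables for which "no data substitution will be applied: self-reported magnitude of symptom change, use of co-interventions, and adverse events". Adherence is not among them. The same section says: "Use of paracetamol rescue medication and intervention adherence will be compared using independent groups *t* tests".

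Under Evaluation of adherence, adherence to both the inserts and the rehabilitation therapy "will be assessed at monthly intervals up to 52 weeks via postal survey". For the inserts, participants report the "number of hours per day and number of days that they have worn their inserts during the previous 4 weeks"; for the exercises, the average days per week over the same period. A month's value is therefore missing when the survey is not returned.

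The Discussion says why the measure matters: "Poor adherence by participants to their shoe insert intervention and/or rehabilitation therapy programme has the potential to confound the study results". It adds that adherence may fall over the 52 weeks. The article gives no rule for counting adherence after a participant is known to have stopped.

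**The concern.** Read together, the general rule and the list of exceptions mean that missing wear time and missing exercise days are imputed before the *t* test. The imputation model has sex, age, baseline scores and group. Adherence has no baseline value because both interventions start at the baseline visit, and neither earlier adherence nor stopping status is a stated predictor. The model cannot tell someone who gave up the insert from someone who mislaid the form.

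Non-return of a self-report survey about wearing an insert may well be related to not wearing it. If so, imputed values for silent participants are too high. At stake is the reading of the trial result: adherence data help to separate an insert that does not relieve pain from an insert that was not worn. Imputation also reports adherence for every randomised participant, so the amount that was never observed is not visible.

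**Working it through.** **Inputs**
- Mean wear among survey returners: 42 h per week. This is the 3-month mean in the earlier case series (Discussion). The article does not say that it is restricted to people still wearing the insert; it is used here only as an illustrative level.
- Share lost: 10%, the dropout rate in the Sample size section. It is the only loss figure in the document.
- Assumption: those lost have stopped, so their true wear is 0. The document does not say this.
- For the simulation only: 45 per arm (half of 90) and a wear-time SD of 15 h (assumed).

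**The plan's own figure.** The article gives no adherence figure to reproduce. The sample size, from which the 10% comes, does reproduce closely. With a difference of 12.5, SD 16.8, two-sided 5% and 90% power, a *t*-based calculation gives 39 per arm; 39/0.9 = 43.3, so 44 per arm and 88 in total, against the stated 90. It is not in dispute.

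**Formulae.** With a share *s* stopped and silent and returners averaging 42 h:
- true arm mean = 42 × (1 − *s*)
- overstatement = 42 × *s*, when the reported mean is 42

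| *s* | True mean (h/week) | Reported | Overstatement (h) | Relative to true |
|---|---|---|---|---|
| 5% | 39.9 | about 42 | 2.1 | 42/39.9 = 1.05 |
| 10% | 37.8 | about 42 | 4.2 | 42/37.8 = 1.11 |
| 15% | 35.7 | about 42 | 6.3 | 42/35.7 = 1.18 |
| 20% | 33.6 | about 42 | 8.4 | 42/33.6 = 1.25 |

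Only the 10% row uses a rate from the document. The 5% row is also what follows if half of that 10% stopped and the other half wore the insert like the returners.

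**Check by simulation.** 2,000 runs, reading the plan's five iterations as five imputations, with group, sex, age and a baseline score as predictors. Mean wear, stiff insert v sham:

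| Stopped and silent | True | Imputed | Observed returns only |
|---|---|---|---|
| 10% v 10% | 37.8 v 37.7 | 42.0 v 41.9 | 42.0 v 41.9 |
| 15% v 5% | 35.7 v 39.9 | 42.0 v 42.1 | 42.0 v 42.1 |
| 20% v 0% | 33.6 v 41.9 | 42.1 v 41.9 | 42.0 v 41.9 |

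Two things follow. With equal silent stopping, both arms are too high by about 4.2 h and no difference is hidden. With unequal silent stopping, the difference disappears (4.2 h at 15% v 5%), but it disappears just as fully in the observed returns. The unequal rates are assumptions with no basis in the document.

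**The case against.** The strongest objection is that imputation is not the cause. In every scenario above the observed returns give the same mean as the imputed data, so the bias comes from informative non-return, which any postal self-report carries. That stands. A reader might infer that the imputation sentence creates the overstatement and that adding adherence to the exceptions would cure it; the calculation shows otherwise. What remains is narrower. The rule as written would replace the months after a known stop with a value near the returners' mean, and its predictors cannot correct for silent stopping.

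Other points on that side also stand:
- A person who has stopped can still return the survey and report zero. Imputed values are drawn from all returners in the arm, not only from people who continued, and because group is a predictor, differences among returners are kept.
- It is tempting to quote larger figures, for example from 30% non-return, or a hidden gap of 6.3 h from 20% v 5% stopping. The document supports none of these rates. It also plans reviews of the rehabilitation at 1 and 12 weeks and monthly telephone reminders afterwards, which may limit silent loss.
- A reader might call the exceptions inconsistent, since co-interventions and adverse events are also collected monthly yet left missing. But the three exempt variables are those analysed by relative risk and risk difference, and the imputed ones are analysed by *t* test or analysis of covariance. That is a coherent split.
- Adherence is not listed among the secondary outcomes, and details of this kind are often left to an analysis plan. The omission of details is not the point here, however: the article states a rule, and the rule covers adherence.

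**Conclusion.** The point holds as a minor one. As written, the protocol imputes missing insert wear and exercise days from a model with no information on stopping, and gives no zero rule after a known stop. If returners average 42 h per week and the 10% dropouts have all stopped, about 42 h is reported where the true mean is 37.8 h, an overstatement of 4.2 h or 11%. If only half of them stopped and the rest wore the insert like the returners, it is 2.1 h or 5%. If non-return is unrelated to stopping, there is no overstatement on average.

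A between-arm difference in adherence is hidden only if silent stopping differs by arm, which the document neither states nor rules out. A reader might infer that the trial's main result is at risk. It is not: the FHSQ pain comparison at 12 weeks does not use adherence. The effect is on how exposure to the insert is reported and how the result is interpreted.

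**What to change.** In the Statistical analysis section:
1. Do not impute insert wear or exercise adherence.
2. Count 0 hours or 0 days from the date a participant is known to have stopped the insert or the exercises.
3. Report the number of surveys returned by arm and month beside the adherence summaries.
4. Add a sensitivity bound with every non-returned month set to 0. In the 10% illustration this bound gives 37.8 h beside the observed 42 h.

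Item 1 alone leaves the mean near 42 h. Items 2 and 4 act on the bias, and item 3 shows how much was not observed. Item 2 needs the stopping date to be recorded when it becomes known.

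The cost is a short change of text and a small extra table. Reported adherence may look less favourable, and the zero bound will be too low if some non-returners kept wearing the insert, so it should be labelled as a bound and not as an estimate.
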